### Measures-Screening and Primary Outcomes

In Table 1, all the assessment and primary outcome measures are described.

**Table 1 table1:** Evaluation tools and methods by outcome of interest.

Primary objective	Description	Evaluation tool
1. Number of participants with virtual reality (VR)–related side effects as assessed by the Virtual Reality Sickness Questionnaire (VRSQ) and the investigators’ observations^a^	Participants in the 2 VR experimental arms (Interventions A and B) are asked to refer to whether the VR head-mounted display was painful, too heavy, or uncomfortable. Participants are asked if they have experienced negative side effects during the VR exposure based on the VRSQ, administered at the end of the VR exposure. This questionnaire is based on a dichotomous answer (Yes/No). During the VR experience, the investigator observes participant reactions and records the behaviors and signs that suggest an unpleasant experience.	VRSQ [44,45]
2. Changes between and within subjects in depression scores^b^	Differences between groups and change from baseline to the T1 and T2 phases in depression scores are assessed based on the Depressive Anxiety Stress Scale-21 (DASS-21-Depression Subscale). Items are answered using a 4-point Likert scale (0-3). Scores range from 0 to 42 (the scores will need to be multiplied by 2 to calculate the final score). Higher scores indicate more severe depression.	DASS-21-Depression Subscale [46-48]
3. Change is being assessed between and within subjects in trait-anxiety scores^b^	Differences between groups and change from baseline to the T1 and T2 phases in trait-anxiety scores are assessed based on the State-Trait Anxiety Inventory-Y2 (STAI-Y2, Trait Anxiety). The measure is a self-report questionnaire investigating trait anxiety based on a 4-point Likert scale (1-4). Scores range from 20 to 80. Higher scores indicate higher trait-anxiety severity.	STAI-Y2 [49-51]
4. Changes between and within subjects in state-anxiety scores^b^	Differences between groups and change from baseline to the T1 and T2 phases in state-anxiety scores are assessed based on the State-Trait Anxiety Inventory-Y1 (STAI-Y1, State Anxiety) before and after each session. The STAI-Y1 is a self-report questionnaire investigating the state anxiety based on a 4-point Likert scale (1-4). Scores range from 20 to 80. Higher scores indicate greater state-anxiety severity.	STAI-Y1 [49-51]
5. Change is being assessed between and within subjects in autonomic arousal, skeletal muscle effects, situational anxiety, and subjective experience of anxious affect^b^	Differences between groups and change from baseline to the T1 and T2 phases in anxiety scores are assessed by the “DASS-21-Anxiety Subscale” based on a 4-point Likert scale (0-3). Scores range from 0 to 42 (the scores will need to be multiplied by 2 to calculate the final score). Higher scores indicate more anxiety severity.	DASS-21-Anxiety Subscale [46-48]
6. Change is being assessed between and within subjects in bodily anxiety sensations^b^	Differences between groups and change from baseline to the T1 and T2 phases in bodily anxiety sensations scores are assessed based on the Self-Assessment Manikin (SAM). The SAM is a nonverbal imagery-based assessment technique used to assess bodily anxiety sensations that directly measure the pleasure, arousal, and dominance associated with a person’s affective reaction to a wide variety of stimuli. Each sensation is assessed on 5 different images distributed in order of size. Participants can tick either of the 5 pictures or 4 spaces in between, making it a 9-point Likert scale. The SAM varies from a minimum score of 3 to a maximum score of 27.	SAM [52]
7. Change is being assessed between and within subjects in levels of chronic nonspecific arousal (stress)^b^	Differences between groups and change from baseline to the T1 and T2 phases in levels of chronic nonspecific arousal (stress) scores are assessed by the “DASS-21-Stress Subscale” based on a 4-point Likert scale (0-3). Scores range from 0 to 42 (the score will need to be multiplied by 2 to calculate the final score). Higher scores indicate a higher level of stress.	DASS-21-Stress Subscale [46-48]
8. Change is being assessed between and within subjects in relaxation levels^b^	Differences between groups and change from baseline to the T1 and T2 phases in relaxation levels are assessed based on the visual analog scale administered before and after each session. This measure assesses relaxation levels before and after each VR experience. Participants had to express how relaxed they felt (0 =not at all relaxed; 10=completely relaxed; 0 =absent; 10=complete). Higher scores indicate higher relaxation levels.	Visual analog scale-relaxation level
9. Change is being assessed between and within subjects in quality-of-life scores^c^	Change from baseline to the T1 and T2 phases in quality-of-life scores on the Psychological General Well-Being Index (PGWBI) is assessed at 3 different assessment times. The measure consists of 22 self-administered items, rated on a 6-point scale (0-5), which assesses psychological and general well-being. Scores range from 0 to 110. Higher scores indicate greater well-being.	PGWBI [53-55]
10. Change is being assessed between and within subjects in coping strategies scores^b^	Change from baseline to the T1 and T2 phases in coping strategies is assessed at 3 different assessment times. The Coping Orientation to the Problems Experienced-New Italian Version (COPE-NVI) is a self-report questionnaire developed to assess the different coping strategies people use in response to stress; it is based on 60 items rated on a 4-point scale (1-4). Total scores range from 60 to 240. Higher scores indicate that a certain coping strategy is frequently used by the person.	COPE-NVI [56]
11. Change is being assessed between and within subjects in sense of presence scores related to the VR and guided imagery experiences^c^	Differences between groups and change from the T1 and T2 phases in sense of presence related to the VR or guided imagery experience are assessed at 2 different assessment times based on a visual analog scale and the ITC-Sense of Presence Inventory (ITC-SOPI). The ITC-SOPI is a self-report questionnaire assessing the sense of presence. Items are rated on a 5-point Likert scale (1-5). Scores range from 36 to 180. To obtain the scores for each of the scales, the average of the items is calculated. Higher scores indicate a higher sense of presence.	ITC-SOPI [57]; Visual analog scale-sense of presence
12. Change is being assessed between and within subjects in heart rate^b^	Differences between groups and change from baseline to the T1 and T2 phases in heart rate are assessed based on the Xiaomi Mi Band 2 sensor. It is used in 3 different assessment times (T0, T1, T2). During T1 and T2 heart rate is measured before, during, and after the in-presence relaxation session.	Xiaomi Mi Band 2 tool [58,59]

^a^T1 (day 7) phase.

^b^T0 (baseline), T1 (day 7), and T2 (day 14) phases.

^c^T1 (day 7) and T2 (day 14) phases.

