**Objective:**

The main aim of this pilot study protocol is to investigate the impact on state anxiety of PMRT, associated with a personalized relaxing scenario in VR, and the role of VR scenarios in facilitating the recall of relaxing images and a sense of presence. A secondary aim is to understand if relaxing sessions administered via Zoom are more effective for managing anxiety and stress than a procedural setting based on audio-track guidance.

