### Study Overview and Objectives

The purposes of the present research project are as follows:

Investigating if PMRT associated with a personalized relaxing scenario in VR can facilitate relaxation and lower state anxietyUnderstanding if the VR scenario helps recall the relaxing image assessed during the follow-up sessionInvestigating if VR is more effective in promoting the association between the relaxing scenario and PMRT than the standard procedure, consisting of PMRT associated with the imagery-induced exposure to a subjective relaxing environmentAnalyzing if the relaxing sessions administered via Zoom are more effective in managing anxiety and stress than a procedure administered via audio-tracks.

We hypothesize that VR would be more effective than GI in promoting relaxation and decreasing state anxiety because it would facilitate the visualization process, allowing individuals to have more realistic sensory experiences than imagery-induced exposure.

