### Power Calculation

Sample size estimation was computed with G*Power 3.1 software (Heinrich Heine Universität Düsseldorf) [43]. As a statistical test, the repeated-measures ANOVAs between factors have been considered. The effect size was set as 0.25, the α as .05, and the Power (1β error probability) as 0.80. We have 3 separate groups and 3 measurements. On the basis of these parameters, we estimated having to recruit at least 36 participants for each of the 3 groups.

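### Table 1 labels twelve unranked outcomes as primary, although the stated aim centres on state anxiety and the sample size supports one F test at .05

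*Protocol article*

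**What the plan says.** - **Outcome list.** The Measures-Screening and Primary Outcomes section says "In Table 1, all the assessment and primary outcome measures are described". The first column of Table 1 is headed *Primary objective* and has twelve numbered rows: VR side effects, DASS-21 depression, trait anxiety, state anxiety, DASS-21 anxiety, SAM, DASS-21 stress, relaxation, PGWBI, COPE-NVI, sense of presence, and heart rate. The last reads "Change is being assessed between and within subjects in heart rate". State anxiety is row 4. No row has a special standing.
- **Aim.** The abstract's Objective says "The main aim of this pilot study protocol is to investigate the impact on state anxiety of PMRT", and adds the role of VR in recall of images and sense of presence.
- **Hypothesis.** Study Overview and Objectives says "We hypothesize that VR would be more effective than GI in promoting relaxation and decreasing state anxiety".
- **Discussion.** It presents the VR versus GI comparison on state anxiety as a preliminary look at the main objective.
- **Sample size.** Power Calculation says "As a statistical test, the repeated-measures ANOVAs between factors have been considered", then "The effect size was set as 0.25, the α as .05, and the Power (1β error probability) as 0.80", and "We have 3 separate groups and 3 measurements". This gives at least 36 per group. No outcome is named.
- **Analysis.** Statistical Procedure and Data Analysis describes one mixed-design repeated-measures ANOVA for between- and within-subject differences, without distinguishing any outcome.

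**The concern.** Which outcomes are primary is something this article fixes itself, and it fixes twelve. Its aim, hypothesis and power paragraph point to something much narrower. A reader of the final report could not tell from the protocol which result the trial was designed to establish. A chance finding on coping or heart rate would carry the same label as a finding on state anxiety. The conclusions in the abstract say the results will shape a later randomised trial, so a chance finding labelled primary could influence the endpoint of that trial.

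**Working it through.** **1. Reproduce the stated sample size.** Inputs from Power Calculation: f = 0.25, α = .05, power 0.80, k = 3 groups, m = 3 measurements. The correlation between repeated measurements is not given; ρ = 0.5 is assumed. For the between-factors test:

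- λ = f² × N × m / (1 + (m − 1)ρ) = 0.0625 × 108 × 3 / 2 = 10.125
- df = 2 and N − 3 = 105
- Power from the noncentral F at α = .05: 0.809. At N = 105 it is 0.797, so 108 (36 per group) is the smallest balanced N that reaches 0.80.

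The stated figure is reproduced. It depends on ρ: power at 108 is 0.891 at ρ = 0.3 and 0.729 at ρ = 0.7. It is the power of **one** test at full α.

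**2. Count the comparative outcomes.** Row 1 (VR side effects) is collected only in the two VR arms, which leaves eleven. The visit descriptions under Study Design do not fully support eleven: COPE-NVI is listed only at T0, and SAM at no visit. Without those two, nine remain. At T1 the ITC-SOPI goes only to the VR participants; dropping presence as well leaves eight.

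**3. Chance of at least one false positive.** Assumptions: one test per outcome at .05, no true effects, and any one significant row read as success. For independent outcomes this is 1 − 0.95^k:

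| k | Chance |
|---|---|
| 8 | 33.7% |
| 9 | 37.0% |
| 11 | 43.1% |
| 12 | 46.0% |

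For correlated outcomes, three-group F tests were simulated (36 per group, common correlation r between outcomes, 40,000 runs):

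| r (assumed) | 9 outcomes | 11 outcomes |
|---|---|---|
| 0.3 | 33.1% | 38.0% |
| 0.5 | 28.0% | 31.6% |
| 0.7 | 20.9% | 22.9% |
| 0.9 | 12.9% | 13.8% |

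The protocol gives no correlations, so r is varied over a range. Testing time effects, before-and-after readings, or both presence instruments in row 11 would add tests to this count.

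**4. What keeping all rows primary would cost.** Bonferroni over eleven: .05 / 11 = .0045. At N = 108 and ρ = 0.5, power for each outcome is about 49%. About 59 per group (177 in total) would be needed for 80%.

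**5. What a pairwise primary test would have.** Intervention A versus Active Comparator, 36 per arm, one time point, two-sided t test at .05, d = 0.5 (assumed two-group equivalent of f = 0.25), no covariate: power is about 55%. About 64 per arm would give 80%.

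**The case against.** **No success rule is stated.** A reader might infer that, followed as written, any one of the significant rows counts as a primary success, so that the trial's false-positive rate is 22% to 43%. The document does not support that. It contains no such rule, and the percentages describe a decision rule that the reader has to add. This stands, and the figures are conditional for that reason.

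**It is a pilot.** The article calls itself a pilot and a proof of concept, with another trial to follow, so control of familywise error matters less. This also stands and lowers the severity. It does not remove the point: the same article calls the study a three-armed randomised controlled trial, gives a formal power calculation, and already reports between-group P values.

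**Multiplicity may be left to an analysis plan.** True of an adjustment method or testing order, and their absence is not criticised here. The labelling in Table 1 is a different matter, because it is stated in this text.

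**Some rows may be assessments only.** The introductory sentence to Table 1 mentions assessment as well as primary measures. That reading is possible, but the table does not say which rows are which, and its column heading covers all twelve.

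**Row 1 might be thought a misused efficacy outcome.** It is not: it is worded as a count of participants with side effects, at T1, in the VR arms.

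**The aim is wider than state anxiety.** Correct: the Objective also names recall and presence, and the hypothesis also names relaxation. The secondary outcomes should reflect this.

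**Conclusion.** The point holds as a mismatch within the article: twelve unranked rows labelled primary, against an aim centred on state anxiety and a sample size for one F test at .05. Under the assumed any-one-row reading, the chance of a false primary finding is about 37% to 43% for nine to eleven independent outcomes, falling for eleven outcomes to about 23% at r = 0.7 and 14% at r = 0.9. Even the last is nearly three times the nominal 5%. The stronger claim, that the trial has a primary error rate of this size, is not supported, because no success rule is stated, the correlations are assumed, and the visit schedule does not settle the count. Given the pilot status, this should be fixed; it does not invalidate the design.

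**What to change.** - **Primary outcome.** Name state anxiety (STAI-Y1) as the single primary outcome, tested once at .05 with the three-group, three-measurement between-factors ANOVA used for the sample size. Because STAI-Y1 is taken before and after the sessions, say which reading at T1 and T2 enters the three measurements. N stays at 108 and the stated power still applies (80.9% at ρ = 0.5).
- **If a pairwise contrast is preferred.** If Intervention A versus Active Comparator becomes the primary test, restate its power: about 55% at 36 per arm under the assumptions above.
- **Other rows.** Label rows 2, 3 and 5 to 12 secondary, with presence and relaxation as key secondaries. Report them with estimates and 95% confidence intervals, or Holm-adjusted. Report row 1 as descriptive tolerability in the VR arms.
- **Disclosure.** Base the choice on the aim and hypothesis already stated, and date it in the registry. Disclose that the Results section had already compared T1 state anxiety between VR and GI in about 40 participants (reported P<.001).

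**Cost.** A relabelled table and a dated registry update. The other outcomes can no longer support a primary claim. The primary outcome is also named after an interim look at the same measure; disclosure makes that visible but cannot undo it.

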### Statistical Procedure and Data Analysis

Quantitative statistical analyses will be performed using SPSS (versions 27.0 and 28.0; IBM Corp) [60,61] and R package [62]. To investigate the normal data distributions of the dependent variables, ranges of skewness and kurtosis will be determined. The Kolmogorov-Smirnov and the Shapiro-Wilk tests will also be performed to evaluate the statistical significance (mean, 95% CI) and normality of the distributions. In addition, Cronbach α will be assessed for each self-report questionnaire’s subscales. To explore sociodemographic features, frequencies, means, and SDs will be measured.

To examine differences between and within subjects, the 3 groups will be evaluated by a repeated-measures ANOVA for mixed designs, where individuals will be the random effect, while the type of intervention and time (T0/T1/T2/before and after each session) will be the fixed effects. The Akaike information criterion and binary logistic regression will be performed to explore significant influence factors.

Spearman rank correlation coefficient will be used to investigate the relationship between the self-reported measures and heart rate.

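### The SAM outcome is given one 3-27 range, which implies an unsigned total of pleasure, arousal and dominance in which a relaxation effect can be partly or wholly offset

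*Protocol article*

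**What the plan says.** Outcome 6 in Table 1 (section Measures-Screening and Primary Outcomes) stands under the column header for primary objectives and reads "Change is being assessed between and within subjects in bodily anxiety sensations". The tool is the SAM, described as a set of pictures "that directly measure the pleasure, arousal, and dominance associated with" a person's affective reaction. On the response format the row says "Each sensation is assessed on 5 different images distributed in order of size" and "Participants can tick either of the 5 pictures or 4 spaces in between, making it a 9-point Likert scale". It closes with the only score it defines: "The SAM varies from a minimum score of 3 to a maximum score of 27".

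The row does not say what a high score means, whether any rating is reversed, or whether the three dimensions are analysed one by one. The section Statistical Procedure and Data Analysis adds nothing specific to the SAM. It states in general that "the 3 groups will be evaluated by a repeated-measures ANOVA for mixed designs".

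**The concern.** A single 3-27 score labelled as bodily anxiety should rise when bodily anxiety rises. If each rating is coded by its name (higher means more pleasure, more arousal, more dominance), the three parts do not point the same way. A session that relaxes people should lower arousal and raise pleasure, and these movements pull the total in opposite directions. The total could then stay nearly flat although the session worked as intended, or move with a sign that nobody can interpret.

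The absence of a stated direction stands out within the table. The rows for depression, trait anxiety, state anxiety, DASS-21 anxiety, DASS-21 stress, relaxation, well-being, coping and presence all say what a higher score means. Of the ten rows that use a scored scale, the SAM row is the only one that does not.

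There is also a question of construct. Of the three dimensions, arousal is the one closest to bodily anxiety. Pleasure and dominance are different aspects of affect, so a total carries the label on one of its three parts.

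**Working it through.** **Inputs from the documents.** Three dimensions; nine points per dimension; score range 3 to 27 (all Table 1, outcome 6); 36 participants per group (Power Calculation).

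**Step 1: reproduce the stated range.** Possible totals of three ratings:

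| Coding of each rating | Minimum total | Maximum total |
|---|---|---|
| 1 to 9 | 3 × 1 = 3 | 3 × 9 = 27 |
| 0 to 8 | 3 × 0 = 0 | 3 × 8 = 24 |
| 1 to 5 (pictures only) | 3 × 1 = 3 | 3 × 5 = 15 |

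Only the unweighted sum of three 1-9 ratings gives 3 to 27. A single dimension would run from 1 to 9. The range is therefore arithmetically correct, and it is the range of a sum.

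**Step 2: what the range does not settle.** Reversing a 1-9 rating replaces x by 10 - x, which again runs from 1 to 9. The total stays at 3 to 27 whichever ratings are reversed. Each of three ratings can be coded in two directions, so there are 2³ = 8 codings. In two of them all three ratings point the same way. In the other six, one rating opposes the other two. The stated range fits all eight.

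**Step 3: raw points (assumed shifts).** Write P, A and D for the shifts in pleasure, arousal and dominance. The raw total moves by P + A + D; the total with arousal reversed moves by P - A + D.

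| P | A | D | Raw total | Arousal reversed |
|---|---|---|---|---|
| +1 | -1 | 0 | 0 | 2 |
| +1 | -1 | +1 | 1 | 3 |
| +0.5 | -1.5 | +0.5 | -0.5 | 2.5 |
| +1 | -2 | +1 | 0 | 4 |

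With equal shifts in all three dimensions, one third of the signal remains. Full cancellation needs particular magnitudes.

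**Step 4: standardised size (assumed shifts).** Take P = +0.5 SD and A = -0.5 SD, equal SDs and independent dimensions. The SD of the sum is then √3 times the SD of one rating, so d = (0.5 - 0.5 + D)/√3.

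- D = 0: d = 0
- D = 0.25: d = 0.25/1.732 = 0.14
- D = 0.5: d = 0.5/1.732 = 0.29
- Arousal alone: 0.5 in size

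For scale, consider a simple two-group comparison with 36 per group and two-sided 5% level. Power is about 9% at 0.14, 23% at 0.29 and 55% at 0.5. This is not the planned repeated-measures ANOVA; it only shows what the loss would mean at this sample size.

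**Step 5: sensitivity to independence.** Suppose pleasure, dominance and reversed arousal correlate at r with one another. The variance of the raw sum becomes 3 - 2r. At r = 0.5 this is 2, and D = 0.5 gives d = 0.5/1.414 = 0.35. The picture is much the same.

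**The case against.** The strongest reply is that a range is only a range. The article never says that the three ratings are added, nor that the total is the analysed variable. Elsewhere Table 1 gives a whole-instrument range for tools it reads by scale: the ITC-SOPI row gives 36 to 180 and then says each scale is an item average, and the COPE-NVI row gives 60 to 240 but interprets the score strategy by strategy. The SAM row itself describes rating each sensation on its own. The full protocol or the cited scoring source may specify aligned coding, and a condensed article may leave item coding to such a document. Finally, the SAM is one of twelve outcomes, and the main aim and hypothesis concern state anxiety.

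Much of this stands. A reader might infer that the analysed outcome is a total in which the effects of relaxation cancel. The documents do not support that: they do not name the analysed variable, they are silent on coding, and reverse coding would leave the range unchanged. The shifts used above are assumptions, and total cancellation is a special case.

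Two things remain. The ITC-SOPI and COPE-NVI rows contain words that point to scoring by scale, and the SAM row has none about its score, so the 3-27 total is the only score the article offers for this outcome. And that score is given without a direction, in a table that supplies one for every other scored scale. This is scoring that the article states, and it is more than a detail left out.

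One further concession: an aligned total need not be weaker than arousal alone. Under the assumptions of step 4 with arousal reversed, d = (0.5 + 0.5 + D)/√3, which is 0.58 to 0.87. The case against an aligned total is what it measures, since a change could come from pleasure or dominance without any change in bodily arousal.

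**Conclusion.** The point holds in conditional form. The stated 3-27 range implies an unweighted total of pleasure, arousal and dominance, with no stated direction or reverse coding, and this total cannot be read as a bodily anxiety score as it stands. If arousal is not reversed and the total is analysed, a relaxation effect is partly or wholly offset. In the illustration, 0 to 0.29 SD is left in the total, against 0.5 SD in arousal alone. That size rests on assumed shifts, equal SDs and independent dimensions. If arousal is reversed, the offset disappears but the mixture of constructs remains.

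The consequence is limited to this one outcome. State anxiety on the STAI-Y1, which carries the main aim, is untouched, and so is the sample size calculation. It is a cheap improvement worth making before the final analysis, so that the coding is not chosen after the results are seen; the article already reports preliminary group comparisons, though none on the SAM.

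**What to change.** In Table 1, outcome 6, replace the 3-27 total with three separate scores of 1 to 9. Name arousal as the score for bodily anxiety, state for each dimension what a higher value means, and report pleasure and dominance as supporting results.

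The same ratings are collected, so the change is one of wording and scoring, and data already gathered can be re-scored if the individual ratings were kept. The downside is three scores to report instead of one. Stating only the coding of an aligned total would cure the missing sign but would leave a score that mixes bodily arousal with two other dimensions.
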